#### Participant timeline

The participant timeline is summarised in figure 1.

**Figure 1 F1:**
[figure not shown]
Diagram demonstrating the participant Timeline. EQ-5D-5L, EuroQol 5-Dimension 5-Level; GAD-7, Generalised Anxiety Disorder-7; K-BILD, Kings Brief Interstitial Lung Disease Questionnaire; mMRC, modified Medical Research Council; PAM, Patient Activation Measure.

#### Sample size calculation

A power calculation was conducted using data from our clinical service at ICHT and data from the INMARK^18^ and INJUSTIS^17^ studies.

Retrospective analysis of our clinical service from 2019 reported spirometry was available at 79% of 131 appointments. (Data from 2019 were selected rather than more recent data as the authors were concerned that spirometry availability was disproportionately lower in 2020 and 2021 due to the impact of the COVID-19 pandemic).

Previous studies have shown high rates of adherence to daily and weekly home spirometry. Median adherence to weekly spirometry in the INMARK study was 96%.

The power calculation estimated that a sample of 108 participants would be large enough to detect a standardised effect size of 0.30 (Cohen’s w) between the active arm and usual care with 80% power. The rate of completion of the 12-month observation period in this study is estimated to be 82% (based on the completion rate of the 52-week INMARK study). Therefore, a total of 132 participants will be recruited to ensure that 108 complete the study.

#### Assignment of arms

Participants will be randomised using a random sequence, random block number randomisation schedule provided by an independent centralised electronic randomisation service (Sealed Envelope) Randomisation will be stratified by the ILD-GAP stage and whether the referring hospital is a secondary or tertiary care centre for ILD as this may affect the availability of formal lung function assessment within a lung function laboratory. ILD-GAP stage is calculated using the participants’ ILD diagnosis, age, sex and physiology and is associated with risk of mortality^35^ and has, therefore, been used here as a measure for severity of disease.

The study is not blinded to either participant or clinician.

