### Study design

The study design is an unblinded randomised control study with parallel arms where participants will be randomly allocated (1:1) to either the remote monitoring arm or usual care arm.

Following informed consent, baseline clinical data collected as part of usual clinical National Health Service (NHS) care will be used for the purpose of the study including previous medical history, all medication usage, previous lung function tests and radiology results. All participants will be asked to complete HRQoL questionnaires (modified Medical Research Council (mMRC) dyspnoea scale, K-BILD Questionnaire, EuroQol 5-Dimension 5-Level (EQ-5D-5L) questionnaire, Generalised Anxiety Disorder-7 (GAD-7) questionnaire) and Patient Activation Measure (PAM) at baseline.

Participants will then be randomly allocated to either the remote monitoring arm or usual care arms.

Remote monitoring arm:

Participants who are allocated to the active remote monitoring arm will be provided with a portable handheld spirometer (Spirobank Smart, MIR, www.spirometry.com) and pulse oximeter (model 3230, Nonin; www.nonin.com) linked to an electronic health application (patientMpower, www.patientMpower.com). Participants will be trained to undertake remote spirometry and pulse oximetry and they will be asked to perform measurements three times per week including two spirometry blows and one resting pulse oximetry reading on each occasion. All readings will automatically be captured via the patientMpower electronic health application and will be immediately visible to their clinical care team via a secure web-based portal. All spirometry attempts will be analysed in real time using artificial intelligence software (ArtiQ, www.artiq.eu)^29^ to assess the quality of the spirometry according to European Respiratory Society (ERS)/American Thoracic Society (ATS) criteria^20^ provided with real time feedback given to participants. Participants will be reminded to record their measurements once weekly.

Participating centres will be asked to monitor these remotely recorded measurements at least every 2 weeks and at, or before, planned clinical assessments. They will be advised that should there be a sustained decrease in either spirometry or pulse oximetry further clinical assessment is recommended.

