#### Data analysis plan

The objective of the primary analysis is to determine if the availability of spirometry within 2 weeks of the date of the first and last clinical review within the observation period is independent of the method by which it was obtained (ie, usual care with remote monitoring of spirometry or usual care alone). The primary endpoint variable is the number of outpatient clinical reviews for which spirometry data are available in the 2 weeks prior to the review. The primary endpoint will be assessed at the first and last outpatient clinical review in all patients who have ≥2 clinical reviews during the study observation period. The primary endpoint will be assessed by a χ^2^ test of independence.

All other endpoints will be summarised for descriptive statistical display.

The health economic analysis will be performed adopting the perspective of the NHS and Personal Social Services. NHS healthcare resource utilisation will be assessed using the data from the study and using standard unit cost data (Personal Social Services Research Unit), staff cost time and NHS tariffs. Effectiveness will be measured in terms of differences in quality-adjusted life-years in the two arms, using a linear approximation method, assuming the change in the utility over time is linear. Costs and effectiveness in both arms will be compared and the results presented in terms of incremental cost-effectiveness ratio.

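### The primary χ² test ignores the factors used to stratify randomisation; a stratified test would be better calibrated and slightly more powerful, at almost no cost

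*Protocol article*

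**What the plan says.** Allocation (Protocol article, Assignment of arms): "Randomisation will be stratified by the ILD-GAP stage and whether the referring hospital is a secondary or tertiary care centre for ILD". The reason follows in the same sentence: "as this may affect the availability of formal lung function assessment within a lung function laboratory". ILD-GAP stage is included as a measure of disease severity; no link to spirometry availability is stated for it. The ratio is 1:1 (Study design).

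Endpoint (Data analysis plan): "The primary endpoint variable is the number of outpatient clinical reviews for which spirometry data are available in the 2 weeks prior to the review". It is assessed at the first and last review, so each patient contributes 0, 1 or 2.

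Test (Data analysis plan): "The primary endpoint will be assessed by a χ^2^ test of independence". That section names neither stratification factor.

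Size (Sample size calculation): 108 evaluable participants are said to be "large enough to detect a standardised effect size of 0.30 (Cohen’s w) between the active arm and usual care with 80% power". With 82% completion this becomes 132 recruited.

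**The concern.** Stratified randomisation holds the mix of centre types, and of ILD-GAP stages, nearly equal between the arms. Variation in availability between strata then contributes almost nothing to the observed difference between arms. An unstratified χ² test still counts that variation as random error. If centre type predicts availability, the test's null variance is too large: it rejects a true null less than 5% of the time and gives up some power.

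The design uses a factor because it may bear on how spirometry is obtained, and the analysis then discards it. A χ² test of independence cannot carry strata or covariates. This is therefore a choice the article has made, not a detail left open for a later analysis plan. What is at stake is calibration and efficiency. Bias and false positives are not at issue.

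**Working it through.** **1. The plan's own figures.** Power of a χ² test with noncentrality N·w², at w = 0.30 and α = 0.05 (α is not stated in the article, so it is assumed):
- 1 df needs N = 88, 2 df needs N = 108 and 3 df needs N = 122.
- At N = 108 and 2 df the noncentrality is 108 × 0.09 = 9.72 and power is 80.4%.

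The stated 108 therefore matches an unadjusted 2×3 table (arm by 0, 1 or 2 reviews). Then 108/0.82 = 131.7, which rounds up to 132. Both figures reproduce.

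**2. Inputs the article does not give.** The centre-type gap in availability is assumed to be 0 to 38 percentage points around a mean of 79%. That mean is the article's 2019 figure from one clinical service, used here as an average over both centre types. The strata are taken as equal in size. For the remote arm, 96% is a working rate; the article reports it as median adherence to weekly spirometry in an earlier study.

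**3. Size of the conservatism, one review per patient.** Total variance is 0.79 × 0.21 = 0.1659. With gap g, the between-stratum part is (g/2)², a fraction f of the total. With balanced strata, the unstratified test at nominal 5% has a true level of about 2[1 − Φ(1.96/√(1 − f))].

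| Gap (tertiary/secondary) | (g/2)² | f | 1.96/√(1 − f) | True level |
|---|---|---|---|---|
| 10 (84/74) | 0.0025 | 0.015 | 1.975 | 4.8% |
| 20 (89/69) | 0.0100 | 0.060 | 2.022 | 4.3% |
| 26 (92/66) | 0.0169 | 0.102 | 2.068 | 3.9% |
| 30 (94/64) | 0.0225 | 0.136 | 2.108 | 3.5% |
| 38 (98/60) | 0.0361 | 0.218 | 2.216 | 2.7% |

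Simulation with 27 patients per stratum per arm agrees: 4.9%, 4.4% and 3.9% to 4.0% at gaps of 10, 20 and 26 points, against about 5% for the stratified test.

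**4. The planned 0/1/2 endpoint.** Simulation of 108 patients, two equal centre strata balanced 1:1, 40,000 trials per scenario, comparing the unstratified 2×3 χ² test with the general-association Cochran-Mantel-Haenszel (CMH) test.

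Type I error with a within-patient correlation of 0.3 (unstratified v stratified): 4.7% v 4.8% at 10 points, 4.4% v 4.9% at 20, 3.8% v 5.0% at 30 and 2.9% v 4.8% at 38. With uncorrelated reviews both tests start near 4% even with no gap, and they separate in the same way (2.4% v 4.6% at 38 points).

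Power with the effect set to w = 0.30 (unstratified v stratified). Ranges of gain cover correlations of 0 and 0.3; the pairs shown are for 0.3.

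| Gap | Centre type matters in usual care only | Centre type matters in both arms (common odds ratio) | Range of gain |
|---|---|---|---|
| 10 | 83.3% v 83.2% | 83.1% v 83.1% | about nil |
| 20 | 83.6% v 84.1% | 84.1% v 85.3% | 0.5 to 1.9 points |
| 30 | 84.9% v 86.4% | 85.4% v 88.3% | 1.5 to 4.3 points |
| 38 | 86.6% v 88.9% | 86.7% v 91.1% | 2.3 to 5.5 points |

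**5. At the article's working rates.** One review, 54 per arm, mean 79% in usual care v 96% in the remote arm. With a 92/66 gap in usual care and 96% at both centre types in the remote arm, power is 81.3% unstratified v 82.6% stratified, a gain of 1.3 points. Exact balance will not survive loss to follow-up: with 18% random loss the figures are 81.2% v 81.7%, a gain of 0.5 points. At an 84/74 gap the difference is within about 0.4 points even with full balance.

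ILD-GAP stage was not simulated. It could add to the loss if it predicts availability.

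**The case against.** The strongest reply is that nothing here is invalid. A conservative test controls type I error and leaves the comparison of arms unbiased. The trial was sized for the unadjusted test, and its 80% power at w = 0.30 stands. All of that is right. A reader might infer that the trial is underpowered or that 108 is wrong; the documents do not support this, because the figure reproduces and every simulated unstratified power at w = 0.30 is above 80%. Scenarios can be built where power is far lower, such as 57% for 79% v 93% mean availability at one review. Those have w near 0.20, so the shortfall comes from the smaller effect, with only about 3 points due to the missing strata.

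The reply also has force on the wording. The article says that centre type may affect laboratory lung function. It does not say that centre type determines the primary outcome, and in the remote arm home readings also count. The effect of centre type may therefore be confined largely to usual care, which puts the loss at the lower end. A reader might also infer that the reported error bars would be wrong, but the section specifies a test and no interval.

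Finally, covariate-adjusted logistic regression is not an obvious remedy: with availability near 96%, cells may hold too few failures for a stable fit. That argues for a stratified contingency-table test, not for ignoring the strata. What remains is that the mismatch between allocation and analysis is real and that removing it costs almost nothing.

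**Conclusion.** The point holds as a modest one. Randomisation is stratified, one factor is justified by its possible effect on access to lung function testing, and the fixed primary test ignores both factors. If a factor predicts availability, the test is valid but conservative and somewhat less powerful than a stratified analysis.

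The power loss is about nil for centre gaps up to 10 points (type I error about 4.9%), about 0.5 to 2 points at 20 (about 4.4%), and about 0.5 to 5.5 points at 26 to 38 (about 4.0% down to 2.9%). The lower ends apply if centre type matters only in usual care or if drop-out erodes the balance. The sizes rest on assumed gaps, equal strata, a mean of 79%, α = 0.05 and centre type alone. The direction does not depend on them. The sample size needs no change.

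**What to change.** In the Data analysis plan, replace the χ² test of independence with a CMH test stratified by centre type and ILD-GAP stage. Use the general-association form if the 0/1/2 count per patient is kept, since that matches the 2-df test for which 108 was derived. State in advance how ILD-GAP stages are merged when a cell is sparse. Report the stratified difference in availability between arms with a 95% CI.

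Cost: slightly more analysis work, and a merging rule that must be fixed before outcome data are analysed. Both factors are already recorded at randomisation, so no new data and no extra participants are needed. Where the strata turn out not to matter, almost nothing is lost: with no centre gap, the simulated power of the stratified test was at most 0.5 points lower.

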#### Data collection and management

All clinical data will be collected on an eCRF provided by REDCap hosted by Imperial College Healthcare NHS Trust.^36 37^ Recruiting trusts are provided with login details on enrolment.

Participant questionnaires can be answered either on paper and transcribed onto REDCap or participants can be invited directly to answer questionnaires electronically through REDCap.

Data will be stored in REDCap during the duration of the project then downloaded and stored with the sponsor at conclusion of the project.

#### Data analysis plan

The objective of the primary analysis is to determine if the availability of spirometry within 2 weeks of the date of the first and last clinical review within the observation period is independent of the method by which it was obtained (ie, usual care with remote monitoring of spirometry or usual care alone). The primary endpoint variable is the number of outpatient clinical reviews for which spirometry data are available in the 2 weeks prior to the review. The primary endpoint will be assessed at the first and last outpatient clinical review in all patients who have ≥2 clinical reviews during the study observation period. The primary endpoint will be assessed by a χ^2^ test of independence.

All other endpoints will be summarised for descriptive statistical display.

The health economic analysis will be performed adopting the perspective of the NHS and Personal Social Services. NHS healthcare resource utilisation will be assessed using the data from the study and using standard unit cost data (Personal Social Services Research Unit), staff cost time and NHS tariffs. Effectiveness will be measured in terms of differences in quality-adjusted life-years in the two arms, using a linear approximation method, assuming the change in the utility over time is linear. Costs and effectiveness in both arms will be compared and the results presented in terms of incremental cost-effectiveness ratio.

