#### Outcomes

The primary outcome will be measured by comparing the number of clinical appointments where recent spirometry is available for review between the remote monitoring and usual care arms. Recent spirometry is defined as within 2 weeks of the clinical appointment. This will be measured at the first and last clinical appointments in the observation period.

The study hypothesis is that participants who have remote monitoring are more likely to have spirometry available for review at their clinic appointments and that the availability of spirometry is therefore dependent on the method of its collection.

Secondary endpoints of the study are as follows:

Service provision:

Number of clinical reviews per patient.Proportion of clinical reviews which are scheduled, patient initiated and clinician initiated.Proportion of clinical reviews which are virtual versus face to face.Number of in-clinic lung function appointments/patient.Number of patients with chest CT scans.

Clinical:

Proportion of patients with ≥10% decrease in forced vital capacity (FVC) (patient-recorded and hospital) of patient-recorded FVC.Change in FVC over time (patient-recorded and hospital).Number of patients starting antifibrotic medication, new immunosuppression and/or oxygen therapy.Patient-recorded dyspnoea score (mMRC score).HRQoL assessed by the EQ-5D-5L,^30^ K-BILD health status questionnaire^31^ and GAD-7.^32^

Adherence to study measurements:

Adherence to study measurements in active arm.Proportion of patients recording measurements on ≥66% of weeks.Patient engagement and activation assessed by the 13-point PAM questionnaire.^33 34^

Health economic:

Nursing/medical time reviewing data portal.Number of patient contacts with/by remote monitoring clinical team.Number of hospital admissions related to respiratory disease.

The study will be evaluated from a health economics perspective to compare NHS resource use in both arms.

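### The plain χ² test does not suit a primary endpoint taken at two reviews per participant; a 1-df participant-level test would answer the stated hypothesis with more power

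*Protocol article*

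**What the plan says.** The Data analysis plan defines the variable: "The primary endpoint variable is the number of outpatient clinical reviews for which spirometry data are available in the 2 weeks prior to the review". It continues: "The primary endpoint will be assessed at the first and last outpatient clinical review in all patients who have ≥2 clinical reviews". The test follows: "The primary endpoint will be assessed by a χ^2^ test of independence".

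The Outcomes section describes the same endpoint in terms of appointments, as "comparing the number of clinical appointments where recent spirometry is available for review between the remote monitoring and usual care arms", and adds: "This will be measured at the first and last clinical appointments in the observation period". Its hypothesis has a direction: "participants who have remote monitoring are more likely to have spirometry available for review at their clinic appointments".

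The Sample size calculation counts participants: "a sample of 108 participants would be large enough to detect a standardised effect size of 0.30" (Cohen's w) with 80% power. It states neither alpha nor degrees of freedom. No section says whether the χ² table holds participants or reviews, or how two reviews from one person are handled.

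**The concern.** Each participant contributes two yes/no results to one plain χ² test. There are two natural ways to build the table.

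- **Participants by count.** Arm against 0, 1 or 2 reviews with spirometry. Participants are independent, so the error rate is sound. But the test has 2 degrees of freedom and treats 0, 1 and 2 as unordered labels. It asks whether the distributions differ in any way, not whether availability is higher.
- **Reviews by availability.** Arm against yes/no over about 216 reviews. Pearson's test assumes that these are independent. Two reviews of one patient share a hospital, its laboratory access and the patient's own habits, so a positive correlation is likely and the test would be too liberal.

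This is the trial's only planned hypothesis test, since all other endpoints are to be described. The trial is also unblinded, so the table should not remain open until the data are in view.

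**Working it through.** **Inputs from the protocol article:** 108 evaluable participants, w = 0.30, 80% power, 82% completion, 1:1 allocation (54 per arm), and 79% availability in the 2019 clinical service. **Assumed, because not given:** two-sided alpha 0.05, within-patient correlation rho, and remote-arm availability. For the last, 96% is illustrative: it is the median weekly adherence cited in the Sample size calculation, not a stated availability rate. The second value, 92%, is a milder case that appears nowhere in the document.

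**1. The plan's own figure.** N = λ/w², where λ is the noncentrality giving 80% power.

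| df | λ | N = λ/0.09 | Power at N = 108 |
|---|---|---|---|
| 1 | 7.849 | 87.21 → 88 | 87.7% |
| 2 | 9.635 | 107.05 → 108 | 80.4% |
| 3 | 10.903 | 121.14 → 122 | 74.8% |

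Only 2 df gives 108. Then 108/0.82 = 131.7, so 132 are recruited, as stated. This points to the 0/1/2 table.

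**2. The 0/1/2 table when availability is equal.** With q = 1 − p, P(0) = q² + rho·pq, P(1) = 2pq(1 − rho) and P(2) = p² + rho·pq. Take p = 0.79 in both arms, so pq = 0.1659.

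- rho 0.2: 0.0773, 0.2654, 0.6573
- rho 0.5: 0.1271, 0.1659, 0.7071

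Mean availability is the same. With d the difference between arms in a cell and e the average of the two arms, w² = Σ d²/(4e) = 0.0061 + 0.0115 + 0.0009 = 0.0185 (0.01845 unrounded). So λ = 108 × 0.01845 = 1.99, and the 2-df test rejects 22% of the time. Simulation (200,000 trials) also gave 22%, with a 1-df trend test at 5%. In the extreme case of rho 0 v 0.7, the 2-df test rejected 87% of the time and the trend test stayed at 5%.

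With equal rho in both arms, the 2-df test's type I error was 4.2–5.0% and the trend test's 5.0–5.1%.

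**3. Power, 54 per arm (simulation).**

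| Availability | rho | 2-df χ² | 1-df trend | Gain (points) |
|---|---|---|---|---|
| 79% v 96% | 0.3 | 90.3% | 94.2% | 3.9 |
| 79% v 96% | 0.5 | 86.0% | 90.6% | 4.6 |
| 79% v 96% | 0.7 | 80.6% | 86.7% | 6.1 |
| 79% v 92% | 0.3 | 58.0% | 67.9% | 9.9 |
| 79% v 92% | 0.5 | 52.6% | 61.8% | 9.2 |

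**4. The pooled review table.** The true variance of an arm's proportion is (1 + rho) times what the test assumes, so type I error = 2 × [1 − Φ(1.96/√(1 + rho))].

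- rho 0.3: 1.96/1.140 = 1.719, giving 8.6%
- rho 0.5: 1.96/1.225 = 1.600, giving 11.0%
- rho 0.7: 1.96/1.304 = 1.503, giving 13.3%

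Simulation at 79% in both arms gave 8.7%, 11.2% and 13.6%.

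**The case against.** The strongest reply is that the endpoint is a number of reviews per patient, the trial is sized in participants, and 108 fits 2 df. On that reading the error rate is sound and the planned power is met, so only a clarification is needed. Most of this stands, and it rules out several stronger readings.

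- **That the primary test inflates type I error.** A reader might infer this from the appointment-level wording in Outcomes. That wording permits pooling but does not specify it, and the sample size points the other way.
- **That the trial is underpowered.** It is not on its own terms: 80.4% at w = 0.30. The low absolute power at 79% v 92% mostly reflects a smaller effect (w of 0.21–0.26).
- **That a significant result would say little about availability.** Under the alternatives examined, a significant 2-df result with the remote arm worse occurred in at most 0.05% of trials. The 87% figure needs an extreme contrast in correlation. The 22% figure needs only a moderate one, and the arms may well differ here: home readings depend on personal adherence, usual care on laboratory scheduling.
- **That small expected counts in the 0 row invalidate the test.** They are common, but no error inflation was found; near the ceiling the test is conservative.
- **That no effect estimate is planned.** An article may leave this to the analysis plan, so it is not counted as a fault.

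The two tables are also not the only possibilities. Separate 1-df tests at the first and last review would fit some of the wording, and 1 df at alpha 0.025 gives N = 106, near 108. Without such a correction, familywise error could reach 1 − 0.95² = 9.75% if the tests were independent.

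What the reply does not answer is that the likely test ignores an ordering that the hypothesis relies on, and that a better test is available at the same N.

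**Conclusion.** The concern holds in a limited form. The analysis that the sample size implies is valid and powered as stated, but it is poorly matched to a directional hypothesis about availability. It can reject when mean availability is equal (22% at rho 0.2 v 0.5). It gives up about 4–6 points of power at 79% v 96% for rho 0.3–0.7, and about 9–10 points at 79% v 92% for rho 0.3–0.5. At w = 0.30, a 1-df test would need 88 evaluable participants rather than 108.

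The pooled table is the less likely reading. If it were used, type I error would be about 9–13% for rho 0.3–0.7, so the wording should exclude it.

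Alpha, rho and the remote-arm rates are assumptions. The match to 2 df is an inference from the arithmetic, not a statement in the document.

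**What to change.** Replace the plain χ² test with a 1-df test that has the participant as the unit. Either of these will serve:

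- a linear-by-linear (Cochran-Armitage) trend test on the 0/1/2 count; or
- equivalently, the difference between arms in mean availability per participant, with a participant-level (cluster-robust) standard error and 95% CI.

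State the unit and degrees of freedom, and say that reviews are not pooled as independent observations. Bring the Outcomes wording into line.

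A logistic GEE with a robust Wald test should not lead. In simulation at 79% v 96% its power was 90.4%, 84.6% and 77.9% for rho 0.3, 0.5 and 0.7. That is no real gain on the 2-df test and below the trend test. In about 1–6% of trials an arm reached 100%, and the log odds ratio could not be estimated.

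The cost is wording and a few lines of code, settled before the outcome data are examined. No extra patients or data are needed, and N = 108 can stand.

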**Methods and analysis:**

132 patients with fibrotic ILD will be recruited and randomised to receive either usual care with remote digital monitoring of home spirometry and pulse oximetry or usual care alone for 12 months. All participants will complete health-related quality of life and experience questionnaires.

The primary outcome compares the availability of spirometry measurements within the 2 weeks preceding planned clinic appointments. Secondary outcomes will explore other aspects of clinical and cost-effectiveness of the remote monitoring programme.

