**Ethics and dissemination:**

The study has been approved by the Camden and Kings Cross Research Ethics Committee (22/LO/0309). All participants will provide informed consent.

This study is registered with www.clinicaltrials.gov (NCT05662124).

The results of the study will be submitted for presentation at regional and national conferences and submitted for peer-reviewed publication. Reports will be prepared for study participants with the support from our public involvement representatives through the charity Action for Pulmonary Fibrosis.

WHAT IS ALREADY KNOWN ON THIS TOPICRegular home spirometry and pulse oximetry are safe and feasible for patients with interstitial lung disease (ILD). However, its utility in supporting clinical decision-making in clinical practice is currently unclear.WHAT THIS STUDY ADDSThis is the first randomised controlled trial of remote monitoring versus usual clinical care in ILD, which aims to establish if there are differences in clinical care and health economic outcomes over a 12-month period.HOW THIS STUDY MIGHT AFFECT RESEARCH, PRACTICE OR POLICYThis study aims to understand whether there is a useful role for remote monitoring in clinical care of patients with ILD and the resource implications required for its incorporation into clinical care.

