### Objectives

The objective of the study is to compare the clinical and cost-effectiveness of remote digital monitoring of home spirometry and pulse oximetry with usual care in the clinical management of patients with ILD.

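### Outside the health economic analysis, the secondary endpoints get descriptive display only, which does not match the objective of comparing clinical effectiveness

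*Protocol article*

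**What the plan says.** The Objectives section states: "The objective of the study is to compare the clinical and cost-effectiveness of remote digital monitoring of home spirometry and pulse oximetry with usual care". The abstract's box on what the study adds says that the trial "aims to establish if there are differences in clinical care and health economic outcomes over a 12-month period". The abstract's methods paragraph is softer: "Secondary outcomes will explore other aspects of clinical and cost-effectiveness of the remote monitoring programme".

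Under Data analysis plan, one endpoint has an inferential method: "The primary endpoint will be assessed by a χ^2^ test of independence". That endpoint is whether spirometry from the preceding 2 weeks was available at the first and last clinic review. The next sentence covers the rest: "All other endpoints will be summarised for descriptive statistical display". A separate paragraph then plans a between-arm comparison of NHS costs and quality-adjusted life-years, reported as an incremental cost-effectiveness ratio.

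Study design has all participants complete mMRC, K-BILD, EQ-5D-5L, GAD-7 and PAM before allocation. K-BILD and GAD-7 are repeated at 3 and 6 months; EQ-5D-5L, PAM and mMRC are repeated at 6 months; and there is a 12-month questionnaire round. The inclusion criteria require in-clinic spirometry within the 6 months before entry, so a baseline hospital FVC also exists. Randomisation is stratified by ILD-GAP stage and by secondary or tertiary centre.

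**The concern.** The tested endpoint records whether a measurement is on file. The remote arm is asked to take that measurement three times a week, so a positive result would say little about whether patients or services fare better. The endpoints that bear on clinical effectiveness are all secondary: FVC decline and change, treatment starts, dyspnoea, health-related quality of life and anxiety. Service use and patient activation are secondary too.

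Followed as written, the plan would give readers summaries by arm. They would see a gap between two means or proportions without being told how precisely it is known, and with any chance baseline imbalance still in it. Stratification does not balance the questionnaire scores directly. The Introduction describes an earlier randomised trial of remote spirometry that missed its quality-of-life endpoint but reported gains in psychological domains. This trial measures K-BILD and GAD-7 repeatedly in both arms, yet plans no estimate that would strengthen or weaken that signal.

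**Working it through.** **Step 1: which endpoints have a comparative analysis.** Setting the Outcomes list against the Data analysis plan:

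- Spirometry availability: chi-squared test.
- Costs and quality-adjusted life-years: compared between arms. EQ-5D-5L is the only utility instrument collected, so it feeds this analysis.
- Reviews, lung function visits, CT scans and respiratory admissions: descriptive as endpoints. The Outcomes section also says NHS resource use will be compared, so such items may enter the cost comparison, but no difference or ratio in the counts themselves is planned.
- K-BILD, GAD-7, mMRC, PAM, hospital FVC change and decline, and treatment starts: descriptive only.
- Patient-recorded FVC, adherence and portal review time: these arise only in the remote arm, so descriptive display is right.

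**Step 2: number available.** From Sample size calculation, 108 completers and 82% completion: 108 / 0.82 = 131.7, rounded up to 132, as stated. With 1:1 allocation and equal loss in the arms, 108 / 2 = 54 completers per arm. (How 108 follows from w = 0.30 is a separate matter and does not bear on this point.)

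**Step 3: precision for a continuous score.** In SD units, the 95% half-width is 1.96 × √(2/54) × √(1 − ρ²), where ρ is the correlation between baseline and follow-up. The document does not give ρ, so a range is shown. √(2/54) = 0.1925, and unadjusted 1.96 × 0.1925 = 0.377. The difference detectable with 80% power at a two-sided 5% level replaces 1.96 by 1.96 + 0.84 = 2.80.

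| ρ (assumed) | √(1 − ρ²) | Half-width (SD) | Variance reduction ρ² | Detectable difference (SD) |
|---|---|---|---|---|
| none (unadjusted) | 1.000 | 0.38 | 0% | 0.54 |
| 0.3 | 0.954 | 0.36 | 9% | 0.51 |
| 0.5 | 0.866 | 0.33 | 25% | 0.47 |
| 0.7 | 0.714 | 0.27 | 49% | 0.39 |
| 0.8 | 0.600 | 0.23 | 64% | 0.32 |

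**Step 4: what that is worth.** An adjusted analysis of 54 per arm is as precise as an unadjusted one of 54 / (1 − ρ²) per arm: 54 / 0.75 = 72 at ρ = 0.5, and 54 / 0.51 = 106 at ρ = 0.7. The scores needed for this are already collected.

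**The case against.** The abstract says the secondary outcomes will explore, the trial is sized only for spirometry availability, and the secondary list is long. Declining to test these endpoints is a sound guard against multiplicity. This stands: no tests are asked for, and the detectable differences above show why significance claims would be unwise.

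The article also condenses a fuller protocol, and choice of model or covariates normally belongs in the analysis plan. That stands for detail. But the article does not leave the matter open: it names descriptive display as the method for all other endpoints.

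Three stronger readings are tempting, and the document does not support them.

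- A reader might infer that every secondary endpoint lacks a comparison. The health economic paragraph compares costs and quality-adjusted life-years, so the cost-effectiveness half of the objective is covered.
- A reader might infer that the baseline scores are discarded. Nothing says so. Quality-adjusted life-years by linear approximation would ordinarily start from baseline utility, and a descriptive table can show change from baseline. What is absent is any planned use of the scores for adjustment.
- A reader might infer that the trial cannot meet its objective. Summaries by randomised arm allow an informal comparison, and the text does not forbid differences or intervals; it names none.

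**Conclusion.** The point holds for the clinical, patient-reported and service secondary endpoints outside the health economic analysis. The stated method, descriptive display, falls short of an objective to compare clinical effectiveness and of a claim to establish whether differences exist, because the one tested endpoint is a process measure. This is a mismatch between aim and method that should be put right; it does not threaten the primary analysis.

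For continuous scores, an unadjusted difference would carry a 95% half-width of about 0.38 SD, and baseline adjustment would bring this to 0.33 to 0.27 SD. These figures assume 54 completers per arm and a correlation of 0.5 to 0.7. At 0.3 the gain is small (0.36 SD). The case for reporting estimates with intervals does not depend on the correlation; only the gain from adjustment does.

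**What to change.** Replace the descriptive-only sentence. For each secondary endpoint measured in both arms, report the between-arm difference with a 95% confidence interval, labelled exploratory and without significance claims:

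- K-BILD, GAD-7, PAM and hospital FVC: ANCOVA or a mixed model, adjusted for the baseline value and the two stratification factors.
- mMRC: a method suited to an ordinal scale, adjusted for the baseline grade.
- Counts (reviews, lung function visits, admissions): rate ratios with follow-up time as offset.
- Proportions (FVC decline of 10% or more in hospital measurements, treatment starts, patients with a CT scan): risk differences.

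Keep descriptive display for endpoints that exist only in the remote arm. If the sponsor prefers to keep descriptive display throughout, the alternative is to narrow the clinical-effectiveness wording in Objectives and in the summary box.

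The cost is modest extra analysis work. No new data or patients are needed, and 108 and 132 stay as they are.
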